### Blinding

The control group will also be provided with an educational intervention that is not related to the main objective of the research, and since the control and intervention groups are assigned into two separate industries, the workers will be unaware of the group assignment. Since the participants will be assigned a code, data and outcome analysis will be unaware of the names of the participants and the control and intervention groups. The main researcher of the study will not be blinded.

There are no known circumstances in which emergency unblinding would be required; however, if there are compelling reasons, such as if the information is needed for recruitment purposes, the principal investigator will provide permission for unblinding. The protocol deviation form should be registered in the trial database.

Participants’ personal information is assigned a unique identification code, stored in a password-protected format, and accessible only to the principal investigator. Participants cannot be identified in manuscripts, reports, or research-related presentations. Data that will be entered into SPSS will be double checked to promote data quality.

### Instruments

Data collection instruments will include the researcher-made questionnaire based on the SCT constructs, the Nordic questionnaire [44], and the RULA method to assess the risk of upper limb MSDs [45]. The questionnaires will be completed by the two groups before the intervention, 3, 12, and 24 weeks after the educational intervention. Table 3 shows the general characteristics of the aforementioned instruments.

**Table 3 Tab3:** Summary of the instruments used for data collection

Scale	Content	Scoring
Researcher-designed questionnaire	Structures of social cognitive theory	Totally disagree (1) to totally agree (5)
RULA	Rapid upper limb assessment	1 (no need for assessment) to 4 (immediate assessment is required) level
Nordic	Identifying musculoskeletal disorders	1 yes to no 2

### Data analysis

Data analysis will be performed using intention-to-treat analysis in the SPSS ver. 19 software and Bayesian network model. First, exploratory factor analysis will be conducted to assess construct validity after confirming sampling adequacy based on the KMO and Bartlett’s test statistic. Second, the Bayesian network model will be used to determine the variables affecting the use of preventive behaviors for MSDs.

Third, data distribution will be investigated using the Shapiro–Wilk test. Fisher’s exact test will be used for qualitative data; independent *t*-test or Mann–Whitney test will be used to determine the mean score of the studied constructs in two control and intervention groups. Pearson and Spearman correlation tests will be used for parametric data and Kendall rank correlation for non-parametric data. Moreover, to compare the difference between the values obtained before the intervention and 3, 12, and 24 weeks after the intervention in each group, generalized mixed models of repeated measure analysis of variance will be used. Bonferroni’s correction will be used for multiple primary outcomes. The difference between the means of the independent groups will also be calculated at 95% confidence interval. *P*-value < 0.05 will be considered as the statistically significant level. No replacement of study subjects or imputation of missing data will be carried out.

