### Intervention

The intervention protocol focuses on correcting workers’ posture based on RULA by creating a fuzzy system that is helpful in most workplaces, where a large number of workers are exposed to WMSDs due to poor posture at work [42]. Exercises also include stretching and strengthening exercises of the upper limb, focusing more on the neck, hand, and wrist joints. The intervention program will be developed based on the most important predictive constructs of SCT from phase 2 of the study. The recruitment process will continue until the required sample size is reached. The researcher-made questionnaire, the standardized Nordic questionnaire, and the RULA method will be completed prior to the intervention. The intervention arm includes providing an educational intervention through the LBD process during assembly work. This intervention focuses on awareness and acquiring skills to maintain a good body posture at work and perform appropriate stretching exercises based on the most important SCT constructs. The educational content will be based on the latest national and international guidelines for the prevention of WMSDs (facts). The control group will not receive the studied intervention and will be provided them with information about ways to prevent breast cancer. The HSE expert will communicate with the participants during the intervention to teach them how to maintain a proper body posture at work and remind them to adhere to the intervention, and stretching exercises will be taught to them during breaks. Participants will receive phone calls and messages on social networks from the research team in the 12 weeks after the intervention to improve participation and adherence.

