### Sample size

Considering that the average total number of assembly-line female workers is about 500 people, sample size was estimated 217 people using Cochran’s formula and considering the type I error (0.05). However, taking into account the 15% possible dropout, it was estimated 250 people in phase 2.

In addition, according to the study by Amit [43], who similarly used an ergonomic intervention to investigate the body posture and WMSDs in workers, to ensure sufficient power and taking into account 10% dropout, the required sample size of 40 people was calculated for each group in phase 3. This sample size was considered sufficient to test the difference between groups at power (80%) and alpha (0.05).

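### Phase 3 is sized at alpha 0.05 although the plan's own Bonferroni rule tests each of two main outcomes at 0.025, and neither outcome has a primary time point

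*Protocol article*

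**What the plan says.** All references are to the protocol article.

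- **Outcomes** lists two main outcomes: the final RULA posture score and the score for adherence to stretching exercises. Neither carries a time point. Two of the secondary outcomes in the same section do carry weeks 3, 12 and 24.
- **Sample size** (phase 3): "taking into account 10% dropout, the required sample size of 40 people was calculated for each group in phase 3", followed by "This sample size was considered sufficient to test the difference between groups at power (80%) and alpha (0.05". It gives no effect size or standard deviation. It points only to a published study "who similarly used an ergonomic intervention to investigate the body posture and WMSDs in workers", and it makes no allowance for two outcomes.
- **Data analysis**: Bonferroni's "correction will be used for multiple primary outcomes". The following sentences say "The difference between the means of the independent groups will also be calculated at 95% confidence interval" and that P < 0.05 "will be considered as the statistically significant level". Whether that P is adjusted is not said.
- **Instruments** places follow-up questionnaires at 3, 12 and 24 weeks. **Data analysis** uses the same three visits in a repeated-measures model, described as a comparison within each group. Its between-group tests are not tied to a visit.
- **Intervention**: "Participants will receive phone calls and messages on social networks from the research team in the 12 weeks after the intervention".

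**The concern.** There are two linked gaps.

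First, the sample size and the analysis use different thresholds. With two main outcomes, Bonferroni at an overall 0.05 tests each at 0.025. A study sized to reach 80% power at 0.05 has less than that at 0.025, so the stated power is not the power of the analysis that the article prescribes.

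Second, the correction is defined over outcomes but not over visits. With three follow-up visits and none designated primary, each main outcome could be judged at whichever visit turns out favourable. The choice also affects the meaning of a positive result. Weeks 3 and 12 fall within, or at the end of, the 12 weeks of calls and messages; week 24 falls after they stop. An effect at week 3 and an effect at week 24 are different claims, and the article does not say which one the trial is meant to test.

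**Working it through.** **Inputs from the article.** 40 per group, 10% dropout, 80% power, alpha 0.05 (Sample size); 1:1 allocation (Study design); two main outcomes (Outcomes); Bonferroni over primary outcomes (Data analysis); three follow-up visits (Instruments, Data analysis).

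**Assumptions.** The test is two-sided, since sidedness is not stated. The comparison is of two means between individually independent workers. The stated 80% is accepted as correct at 0.05.

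**1. The plan's own figure.** Without an effect size, 40 per group cannot be reproduced from first principles. The dropout step is consistent: 40 × 0.9 = 36 evaluable, and 36 / 0.9 = 40.

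**2. Effect implied by 36 per group at 0.05.** d = (z₀.₉₇₅ + z₀.₈₀) × √(2/n) = (1.960 + 0.842) × √(2/36) = 2.802 × 0.2357 = 0.66. The t-test version gives 0.67.

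**3. Power at the Bonferroni level.** The threshold per outcome is 0.05 / 2 = 0.025, so the critical value is 2.241.

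Power = Φ(1.960 + 0.842 − 2.241) = Φ(0.56) = 71.2%.

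The t-test version gives 70.8%. A one-sided reading gives 70.1%. Under the normal approximation the effect size and n cancel, so the drop from 80% to about 71% does not depend on the unstated effect.

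**4. What 80% at 0.025 would take.**

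- Same n, larger effect: d = (2.241 + 0.842) × 0.2357 = 0.73; the t-test version gives 0.74.
- Same effect, larger n: ((2.241 + 0.842) / (1.960 + 0.842))² = 1.21, so 36 × 1.21 = 43.6, or 44 evaluable, and 44 / 0.9 = 48.9, or 49 per group against the stated 40.

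**5. Error rate, one visit.** Two independent tests at 0.025: 1 − 0.975² = 4.9%. Bonferroni does its job here.

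**6. Error rate if any of three visits could count.** Each test is at 0.025 and the two outcomes are taken as independent.

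| Between-visit correlation | Family-wise error, 2 outcomes × 3 visits |
|---|---|
| 0 | 1 − 0.975⁶ = 14.1% |
| 0.5 | 12.7% (simulated) |
| 0.7 | 11.1% (simulated) |
| 0.9 | 8.5% (simulated) |

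Zero correlation is an upper bound rather than a realistic value for repeated measures on the same worker. Positive correlation between the two outcomes would lower all four rows.

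**The case against.** Several counter-arguments have force.

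- **The significance level.** A reader might infer that P < 0.05 contradicts the Bonferroni sentence. The text does not support this. P < 0.05 can be the overall level, or the threshold for Bonferroni-adjusted P-values. The wording is ambiguous, not contradictory. The 95% intervals are described for group differences in general and are not tied to the primary tests, so they are no contradiction either.
- **Error control.** A reader might infer that the type I error is uncontrolled. It is not: at any single visit Bonferroni holds it at or below 5%. Only selection among visits is open. Testing everything at an unadjusted 0.05 would give a higher rate, but that scenario disregards the Bonferroni sentence and does not describe this plan.
- **No any-visit rule is stated.** Nothing in the article says that success may be claimed at whichever visit is significant, and a repeated-measures model is planned. This stands, and the 8.5% to 14% is therefore conditional. The model does not close the gap, however, because it is worded as a within-group comparison and names no between-group contrast.
- **Condensation.** An article may leave detail to the full protocol, and Table 1 is a figure that could not be read here. But Outcomes does give weeks for two secondary outcomes and none for the main ones. The alpha mismatch lies between two printed sections and does not depend on any unseen document.
- **The 71%.** It rests on an 80% that cannot be verified, and it is per outcome. The chance of success on at least one outcome would be higher and on both lower. It also ignores that, under Sampling, the industrial unit is the unit of randomization. A reader might take 71% as the trial's actual power; it cannot be read that way.

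**Conclusion.** The concern holds in two separate parts.

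1. **Power.** Sample size and Data analysis use different thresholds for the main outcomes. Accepting the stated 80% at 0.05, with a two-sided test and about 36 evaluable per arm, power per outcome is about 71%, or 80% only for a standardized difference of about 0.74 instead of about 0.67. This follows from the Bonferroni step alone and has nothing to do with the missing time point. It is a figure before clustering; allocation by industrial unit can only lower it.

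2. **Time point.** No primary visit is fixed among weeks 3, 12 and 24, and the correction does not extend to visits. If significance at any visit were accepted, family-wise error would be about 8.5% to 14% (between-visit correlation 0.9 to 0, outcomes independent). That measures the room left open; it is not a property of a stated decision rule.

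Whether P < 0.05 is adjusted is a matter of clarity only.

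**What to change.** - **Sample size:** state the effect assumed, and give the power or detectable effect at 0.025, labelled as per outcome and before any allowance for clustering. On present figures that is about 71% for the implied difference of 0.67, or 80% for 0.74. Neither should be presented as the power of the trial as allocated.
- **Outcomes:** prespecify one primary time point for both main outcomes and make the other visits secondary. Week 24 is a natural choice, being the end of the 6-month follow-up and after the 12 weeks of reminders. The choice belongs to the investigators and should be fixed before outcome data are seen.
- **Data analysis:** name the between-group comparison at that visit as the primary test. State that P < 0.05 applies to Bonferroni- or Holm-adjusted P-values for the two primary outcomes and is nominal for secondary ones.

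**Cost:** a few sentences and a less favourable stated power. No extra workers are needed if the lower power is accepted. Restoring 80% per outcome for the same effect would take about 49 per group instead of 40, still before clustering.

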### Dissemination policy

Trial results will be submitted to peer-reviewed journals for publication. Part of the data, such as information regarding the main outcome, can be shared.

## Discussion

The present study focuses on workplace health promotion by investigating the effect of theory-based ergonomic intervention on the preventive behaviors of WMSDs among assembly-line female workers. The main framework of the present study is a theory-based intervention with the aim of maintaining correct body posture at work and performing stretching exercises using the LBD approach in the workplace. Assembly-line female workers undertake a large amount of family and social duties and responsibilities at the same time [46], and it seems that designing appropriate educational interventions can be helpful in promoting correct ergonomic behaviors in these women.

Studies have suggested a revision in the design of educational interventions in workplaces [47, 48]. An educational model directs the program in the right path and reduces the ambiguities in the main content of the intervention and provides a framework for guidance and evaluation in interventions [49]. In the present study, a theory-based educational intervention will be designed in a structured manner, and the LBD approach will be used for workers in their workplace.

Therefore, the scoring system is based on Bayesian network and fuzzy sets. In other studies, these analyzes have yielded a more accurate evaluation on the effectiveness of ergonomic interventions [20]. To the best knowledge of the author, this is the first study that will evaluate the effects of theory-based educational intervention based on Bayesian model and fuzzy sets. On the other hand, other previous ergonomic interventions on the assembly-line workers have not used health education theories [41, 50].

Due to economic problems in the industrial environment, it will not be possible to carry out physical ergonomic interventions in the workplace, such as changing tables and chairs in the assembly halls or using ergonomic tools. In addition, the intervention will only be carried out on assembly-line female workers. Other limitations of the present study include the use of a self-reporting tool that results will be inevitably affected by the memory error, lack of clarity, and individual biases.

This study will evaluate the effect of theory-based ergonomic intervention on the preventive behaviors of MSDs in Northeast Iran. This theory-based ergonomic intervention strategy with a LBD approach, if reported to be effective, may become an important tool to reduce the burden of MSDs, and subsequent disabilities and absenteeism, and increase productivity and job satisfaction of women working in the industrial environments.

### Trial status

This is the first version of the protocol on 24 January 2023. Recruitment is expected to be completed by August 2023.

## Data Availability

Non-applicable participant-level data will not be shared.

## Abbreviations

MSDS: Musculoskeletal disorders
RULA: Rapid upper limb assessment
LBD: Learning by doing
WMSDs: Work-related musculoskeletal disorders
SCT: Social cognitive theory
HSE: Health, safety, and environment
